## Abstract

**Backgrounds/Objectives:** Atrial fibrillation (AF) confers a fivefold greater risk of acute ischaemic stroke (AIS) relative to normal sinus rhythm. Among patients with AF-related AIS (AFAIS), recurrence is common: AFAIS rate is sixfold higher in secondary versus primary prevention patients. Guidelines recommend oral anticoagulation for primary and secondary prevention on the basis of CHA_2_DS_2_-VASc. However, guideline adherence is poor for secondary prevention. This is, in part, because the predictive value of CHA_2_DS_2_-VASc has not been ascertained with respect to recurrence: patients with and without previous stroke were not routinely differentiated in validation studies. We put forth a protocol to (1) validate, and (2) update CHA_2_DS_2_-VASc for secondary prevention, aiming to deliver a CPR that better captures 90-day recurrence risk for a given AFAIS patient. Overwhelmingly poor quality of reporting has been deplored among published clinical prediction rules (CPRs). Combined with the fact that machine learning (ML) and deep learning (DL) methods are rife with challenges, registered protocols are needed to make the CPR literature more validation-oriented, transparent, and systematic. This protocol aims to lead by example for prior planning of primary and secondary analyses to obtain incremental predictive value for existing CPRs. **Methods:** The Virtual International Stroke Trials Archive (VISTA), which has compiled data from 38 randomised controlled trials (RCTs) in AIS, was screened for patients that (1) had an AF diagnosis, and (2) were treated with vitamin K antagonists (VKAs) or without any antithrombotic medication. This yielded 2763 AFAIS patients. Patients without an AF diagnosis were also retained under the condition that they were treated with VKAs or without any antithrombotic medication, which yielded 7809 non-AF AIS patients. We will validate CHA_2_DS_2_-VASc for 90-day recurrence and secondary outcomes (7-day recurrence, 7- and 90-day haemorrhagic transformation, 90-day decline in functional status, and 90-day all-cause mortality) by examining discrimination, calibration, and clinical utility. To update CHA_2_DS_2_-VASc, logistic regression (LR), extreme gradient boosting (XGBoost), and multilayer perceptron (MLP) models will be trained using nested cross-validation. The MLP model will employ transfer learning to leverage information from the non-AF AIS patient cohort. **Results:** Models will be assessed on a hold-out test set (25%) using area under the receiver operating characteristic curve (AUC), calibration curves, and F1 score. Shapley additive explanations (SHAP) will be used to interpret the models and construct the updated CPRs. **Conclusions:** The CPRs will be compared by means of discrimination, calibration, and clinical utility. In so doing, the CPRs will be evaluated against each other, CHA_2_DS_2_-VASc, and default strategies, with test tradeoff analysis performed to balance ease-of-use with clinical utility.

## 1. Introduction

Atrial fibrillation (AF) is the most common cardiac arrhythmia [1] and confers a fivefold greater risk of acute ischaemic stroke (AIS) relative to normal sinus rhythm [2]. AF-related AIS (AFAIS) is reported to account for 13–26% of global AIS burden [3], and its association with greater infarction size, severity, disability, mortality, and cost compared to AIS of non-thromboembolic pathogenesis is well-documented [4,5,6,7,8]. Fortunately, AFAIS is known to be highly preventable with oral anticoagulants (OACs) [9]. Current guidelines recommend OACs for primary and secondary prevention on the basis of CHA_2_DS_2_-VASc [10,11], a prognostic clinical prediction rule (CPR) that estimates annual risk of AFAIS. However, it has been reported that only 32% of AFAIS survivors are prescribed OACs for secondary prevention in a guideline-adherent manner [12,13]. In fact, several studies have shown that patients with higher CHA_2_DS_2_-VASc scores were paradoxically less likely to receive antithrombotic therapy [1,14,15]. While this ‘anticoagulation paradox’ is partly attributable to the fact that a high CHA_2_DS_2_-VASc score implies high bleeding risk [16], there is also concern that OACs are being omitted for non-therapeutic reasons despite RCT evidence substantiating that recurrence rates are highly modifiable with OACs [17]. This is alarming given that 1-year recurrence rates have been reported to be as high as 30% [18,19]. We contend that the absence of research ascertaining the predictive performance and clinical utility of CHA_2_DS_2_-VASc with regard to recurrence is partly to blame. Indeed, it is a major limitation that patients with and without stroke history were not routinely differentiated in studies validating CHA_2_DS_2_-VASc [20]. Rather, validation studies employed numerical scores to divide subjects into risk strata irrespective of whether a score of 4 belonged to a 75-year-old female patient with diabetes or a 60-year-old male with history of hypertension, stroke, and myocardial infarction, for example. Therefore, data on the performance of CHA_2_DS_2_-VASc among cohorts with previous AIS is scarce, and existing studies have reported poor discrimination, with C-statistics generally below 0.6 [21]. This prompted us to design an external validation study for CHA_2_DS_2_-VASc in AF patients scoring ≥ 2 points after having suffered an AIS.

To date, one study has analysed stratum-specific relative risk of mortality associated with unique combinations of C, H, A, D, and S in the since-superseded CHADS_2_ score and found S_3_—assigning 3 points to stroke history—to be a better fit to available mortality data than S_2_ [22]. A more recent study expanded on CHA_2_DS_2_-VASc with additional comorbid features to yield a multi-morbid index that reported that the weight for stroke history should be increased to 19 (out of a total of 44) points [23]. In fact, one well-known ‘blind spot’ of CHA_2_DS_2_-VASc is that a patient with a history of stroke and no other risk factor is assigned a score of 2 corresponding to an annual stroke risk of 2.2–4.5% [24,25], which underestimates recurrence rates. These findings suggest that secondary prevention may merit a bespoke CPR. To this end, we also set out to update CHA_2_DS_2_-VASc to yield a CPR that is better suited to the acute context of AFAIS. We deploy traditional regression as well as machine learning (ML) and deep learning (DL) tools to more aptly capture the relative importances of the constituent features of CHA_2_DS_2_-VASc in the context of early secondary prevention, when the risk of recurrence is highest.

Timing of OAC initiation is a critical aspect of secondary prevention. The early post-stroke period is characterised by a transient state of heightened vulnerability to both thromboembolism and haemorrhage, necessitating individualised assessment of risk of recurrence versus haemorrhagic transformation (HT). At present, the timing of OAC administration is founded on expert opinion and observational data (level C evidence) [26]. Evocative of the absence of consensus was a survey conducted among UK specialists which reported that 95% of respondents were uncertain about optimal timing for novel OAC (NOAC) (re)introduction [27]. This is a consequence of the historical exclusion of AIS patients from major phase III RCTs in the context of stroke prevention in AF (SPAF). Patients were excluded for at least 7 days after AIS in the ARISTOTLE trial (apixaban) [28], 14 days after minor AIS and 90 days after major AIS in the ROCKET-AF trial (rivaroxaban) [29], and 14 days after minor AIS and 180 days after major AIS in the RE-LY trial (dabigatran) [30]. To address this critical gap, four RCTs—ELAN [31], TIMING [32], START [33], and OPTIMAS [34], collectively enrolling over 9000 participants [35]—investigated the timing of NOAC initiation in AFAIS patients. Of these, two trials—ELAN and TIMING—have been completed. The ELAN trial evaluated early NOAC initiation within 2 days for minor strokes and 6 days for moderate strokes, while the TIMING trial assessed initiation within 4 days for minor strokes and 7–14 days for major strokes. The timeframes ELAN and TIMING set for moderate strokes means that the evidence still does not strongly support very early NOAC initiation (e.g., within 1–2 days) for many patients. The ongoing START and OPTIMAS trials adopted flexible approaches also tailored to stroke severity, generally considering both early and delayed strategies within the first 14 days post-stroke. Against this backdrop, the analyses planned herein will be a timely contribution to the body of literature that aims to better understand early AFAIS recurrence patterns and support the selection of patients who are most likely to benefit from very early OAC.

Deploying well-validated CPRs is one way of implementing personalised evidence-based medicine [36]. CPRs are abundant in the biomedical literature, and their publication has proliferated in recent years [37,38]. The publication of at least 731 diagnostic and prognostic prediction model studies on COVID-19 during the first 12 months of the pandemic is a case in point [39]. Although a great many stroke-risk CPRs have been proposed, CHA_2_DS_2_-VASc is well-validated and commonly used worldwide [40,41], and its use has been recommended in clinical guidelines for over a decade [42]. This is the exception rather than the rule among CPRs, as there is a habit of developing more CPRs for the same purpose in lieu of validating existing ones [43]. Newly developed CPRs are thus often based on smaller samples, and information captured within previous cohorts is neglected, running contrary to the principle that inferences should be founded on the cumulative data of as many patients as possible. As a result, there is remarkably little data to suggest a positive impact on the process or outcome of clinical care despite mushrooming CPRs [37].

Clearly, the ability to critically evaluate new CPRs is key, and is predicated on complete and transparent reporting [44]. Yet numerous studies evaluating CPR publications have found them to be poorly conducted and incompletely reported, with pervasive deficiencies in statistical methods and high risk of bias (ROB) [45,46,47,48]. In particular, small datasets, inappropriate imputation algorithms, and inadequate internal validation techniques were common, and major methodological details were frequently missing [49,50,51,52,53,54,55,56,57,58,59,60,61,62,63,64]. The 2015 TRIPOD guideline was born out of necessity for full and clear reporting of CPRs [65]. Its artificial intelligence (AI) extension, TRIPOD+AI, was introduced in 2024 to offer specialised guidance for the unique challenges posed by ML and DL, including overfitting, interpretability, and the risk of embedding biases [44]. In addition, the development of detailed study protocols at the outset of CPR research is increasingly being recognised as crucial to enhancing transparency and peer scrutiny, facilitating reproducibility and cooperation, and mitigating ROB and creative data dredging [66,67,68,69]. TRIPOD+AI features a new section dedicated to open science principles, including item 18c which asks that researchers indicate where the study protocol can be accessed or state that a protocol was not prepared [44]. The 2024 announcement of the TRIPOD-P guideline, which will focus on the preparation of protocols, marks yet another step forward [70]. In the wait for TRIPOD-P, we hope that this protocol will lead by example for the prior planning of primary and secondary analyses for CPR studies.

Overall, our goal is to develop a CPR with superior discriminative performance, calibration, and clear clinical utility for the early secondary prevention of AFAIS. Among the cardiovascular contributors to stroke investigated in the seminal Framingham Heart Study, AF was unique in that its effect on AIS risk did not abate with advancing age [71]. In fact, AF was the sole cardiovascular condition to exert an independent effect on stroke incidence among patients aged 80–89 years. With demographic ageing, prevalence of AF is projected to increase 2.5-fold over the next 40 years [72] and has already been reported to be on a significant incline among acute hospital admissions [73]. Taking these factors in conjunction, a substantial rise in the societal burden of AFAIS may materialise in coming decades [74,75], underscoring the need for improved secondary prevention. As a matter of fact, the dynamic nature of patient demographics suggests that every CPR is subject to an expiration date [76,77], and we argue the time is ripe to challenge the status quo of CHA_2_DS_2_-VASc. Of course, numerous external validation studies and impact studies will be necessary to determine whether the CPR we develop increases physicians’ guideline-adherence or, on the contrary, obfuscates OAC prescription. Additionally, it will be interesting to explore whether the CPR proves useful for other purposes—guiding neurologist referrals, informing recruitment in RCTs, controlling for confounding variables in observational research (e.g., via propensity scores), and educating patients—that indirectly improve secondary prevention [78]. Parenthetically, we hope researchers forgo the habit of continually developing new CPRs before rigorously validating and updating existing ones and adopt the habit of abiding by open science practices such that the literature may become more validation-oriented, transparent, and systematic.

## 2. Methodology

### 2.1. TRIPOD+AI Adherence

Items of TRIPOD+AI that could be met within the confines of a protocol have been addressed. The checklist has been provided in the Supplementary Materials file S2.

### 2.2. Data Source

The Virtual International Stroke Trials Archive (VISTA) is an international, prospective data repository whose Acute subsection (VISTA-Acute) has collated data from 38 RCTs in AIS to date, the methods of which have previously been described [79]. Study timelines including start and end of accrual were unique to each contributing trial and, where available, have been provided in the appending materials. Study setting and geographic location of centres also differed for each trial and have been provided. These data were presented in aggregate because the number of centres implicated was not disclosed. Eligibility criteria for participants have been compiled across the contributing trials and made available in the appending materials, too. The high quality of the VISTA dataset provides an excellent opportunity for analysis of prognostic factors and has already allowed several stroke-risk prediction models to be established and validated [80].

### 2.3. Study Population

The filters applied in screening the repository were that the patient (1) had an AF diagnosis, and (2) was treated with vitamin K antagonists (VKAs) or without any antithrombotic medication. Criterion (2) was informed by the fact that contributing trials predated the introduction of novel oral anticoagulants (NOACs).

This yielded 2763 patients with documented age; sex; pre-stroke modified Rankin Scale (mRS) score; 90-day mRS; baseline National Institutes of Health Stroke Scale (NIHSS) score; 30- and 90-day NIHSS; medical history including congestive heart failure (CHF), hypertension, hyperlipidaemia, diabetes mellitus (DM), myocardial infarction (MI), coronary artery disease (CAD), transient ischaemic attack (TIA), prior AIS, and tobacco use; intravenous thrombolysis with recombinant tissue plasminogen activator (IVT); and onset-to-thrombolysis time (OTT). Medication administration records and adverse event records were also extracted: the former were screened for start and end days of VKA administration relative to AIS and the latter were screened for 7- and 90-day recurrence; 7- and 90-day haemorrhagic transformation (HT); and 90-day mortality.

Patients without an AF diagnosis were also retained under the condition that they were treated with vitamin K antagonists (VKAs) or without any antithrombotic medication. This yielded 7809 patients, whose records documented the same information as above.

The AF cohort will be used for primary and secondary analyses, while the non-AF cohort will serve exclusively for secondary analyses.

### 2.4. Predictor Variables

The predictor variable in the validation analyses is CHA_2_DS_2_-VASc score, computed on the basis of its constituent features. It is computed as follows: 1 point for each of CHF, hypertension, DM, vascular disease (MI, CAD, or peripheral artery disease), age 65–74 years, and sex category (female), and 2 points for each of age ≥ 75 years and antecedents of AIS or TIA [24]. All features were measured at baseline, and, with the exception of age, all were binary encoded. As one of the more subjective items considered by CHA_2_DS_2_-VASc, peripheral artery disease was seldom recorded by contributing trials. Hence, MI and CAD will underlie the vascular disease feature.

The predictor variables in the updating analyses are the constituent features of CHA_2_DS_2_-VASc—omitting S_2_, which provides no discriminatory information in a cohort where all patients inherently have the same value (i.e., 2)—and previous stroke. Crucially, since secondary prevention is, by definition, aimed at patients having sustained an AIS, previous stroke is defined herein as any episode of AIS *prior* to the one that prompted recruitment. Besides preserving the familiar 7-feature structure of CHA_2_DS_2_-VASc, incorporating this variable in the updated CPR is very apropos in the modern-day context of effective treatment and demographic ageing which signify that many patients survive one or more strokes.

### 2.5. Confounding Variables

The measured confounding variables are antithrombotic treatment (VKAs or none), start and end days of VKA administration, IVT, and OTT. Antithrombotic medication, IVT, and the timings of their administration constitute all information available about treatments received by participants.

Actions taken to blind the assessment of predictors or confounding variables in contributing trials, if any, were not recorded by VISTA. Qualifications and demographic characteristics of predictor assessors were not available.

### 2.6. Outcome Variables

The primary outcome variables are 90-day recurrence, defined as any episode of AIS within 90 days of the event that prompted recruitment. Of our 2763 AFAIS patients (and 7809 non-AF AIS patients), some will have no prior history of stroke while others will have suffered antecedents. Thus, our primary outcome variable includes second as well as third or *n*th strokes.

The secondary outcome variables are 7-day recurrence; 7- and 90-day HT; 90-day decline in functional status; and 90-day all-cause mortality. The 7-day recurrence is defined analogously to the primary outcome variable: any episode of AIS within 7 days of the event that prompted recruitment. The 7- and 90-day HT are defined as any episode of intracranial haemorrhage (ICH) within 7 and 90 days of the event that prompted recruitment, respectively.

Decline in functional status is defined as 90-day mRS score ≥ 2 for patients that were not disabled before stroke (pre-stroke mRS 0–1) and failure to return to pre-stroke mRS score at 90 days for patients that were disabled before stroke (pre-stroke mRS ≥ 2). In other words, progression on the scale qualifies as decline in functional status, with the exception of progression from mRS 0 to 1, seeing as even minor residual deficit post-stroke will, by definition, increase an mRS 0 patient to mRS 1.

To account for the fact that death within 90 days may preclude observation of 7- and 90-day recurrence, we will conduct a sensitivity analysis using a Cox proportional hazards model with mortality treated as a censoring event.

All contributing trials were double-blind RCTs, though no further details on blinded outcome assessment were accessible. Qualifications and demographic characteristics of outcome assessors were not available.

### 2.7. Sample Size and Power Analysis

Validating a CPR demands a moderate sample size relative to updating a CPR, which demands a large sample size [78]. Nonetheless, updating a CPR—meaning the predictors are known but not the functional form or model parameters—is still less data-demanding than development from scratch, where even the predictors are unknown. We employed the methods proposed by van Smeden et al. [81,82] and Riley et al. [83] to calculate the required sample sizes for our regression analyses. These methods were formulated to guide power analyses for studies intending to develop models from scratch. They have been encapsulated in a four-step procedure that represents a significant advancement over the historically inconsistent and poorly substantiated rules of thumb regarding the desirable number of events per variable (EPV) [84].

Each of the four steps in this procedure yielded a sample size estimate, with the largest selected as the required sample size. This approach ensured that our sample size was sufficient to accomplish the following goals: (1) estimate the overall 90-day recurrence prevalence with high precision, (2) minimise the mean absolute prediction error, (3) require minimal regularisation, and (4) limit optimism as measured by Nagelkerke’s R^2^. Steps 1, 3, and 4 were implemented using the psampsize package developed by the authors for R [84], while step 2 used the tool available at https://mvansmeden.shinyapps.io/BeyondEPV/ (accessed on 4 January 2024). The calculations—which are based on the estimated prevalence of 90-day recurrence in the target population, the number of predictor variables in our CPR, its anticipated discriminative performance, and the acceptable mean absolute prediction error, among other parameters—have been made explicit in the appending materials. We utilised 90-day recurrence rates within the 0.05–0.25 range, conservatively adopting the rate that produced the largest sample sizes.

The sample sizes derived from steps 1, 2, 3, and 4 were 288, 344, 680, and 459 patients, respectively. We therefore deemed a minimum total sample size of 680 patients necessary for CPR development. Given that our sample size is 2763 patients and the fact that we will perform validation and updating (and not development from scratch), we contend that our regression analyses are adequately powered. Of note, 75% of our dataset (*n* = 2072 patients) will be used for regression model training and the remaining 25% (*n* = 691 patients) will be reserved for testing. The fact our test set alone exceeds the required 680 patients further supports our sample size.

ML and DL techniques are inherently more data-intensive than regression [85]. This is because the number of predictors they consider far exceeds that of regression, even when the same set of predictors is considered, because they examine multiple interaction terms [84]. Unfortunately, guidance for a priori sample size calculations is currently lacking for most ML/DL techniques [86]. However, if closely related data are readily available, it has been suggested that inspecting model learning curves in the related dataset can be valuable to estimate the required sample size for the main dataset [87,88]. We will therefore explore the observed power of our non-regression models by means of learning curves on our non-AF dataset, as well as via a key information theoretic metric: Kullback–Leibler (KL) divergence.

Firstly, we will create multiple subsets from the non-AF dataset (ranging from 500 to 5000 patients, in 500-patient increments) and train our ML models on these subsets. Performance will be evaluated using a fixed test set (25% of the non-AF dataset, *n* = 1952). Learning curves will be plotted to depict performance against training subset size, which will help visualise the point at which performance stabilises, indicating diminishing returns with additional data. If this stabilisation point aligns with the size of the AF dataset training set (*n* = 2072), we will be reassured that our sample size is likely adequate. The similarity between the non-AF and AF datasets, which will have at this stage been assessed via descriptive statistics, will inform the reliability of this inference. Learning curves specific to the AF dataset will be generated to further assess the legitimacy of this inference. This will employ the same process, training ML models on progressively larger subsets of the AF dataset (ranging from 500 to 2000 patients, in 500-patient increments) before plotting performance against training subset size. Importantly, DL models will use an enhanced sample size via transfer learning, leveraging 7809 non-AF patients during pretraining. This strategy is beneficial because it addresses the power law that has been observed for large neural networks, whereby performance improves according to *y* = *x*^a^, with *a* < 0 [89], implying that as the number of training samples (*x*) increases, the generalisation error (*y*) decreases at a slowing rate.

KL divergence will be used to assess the generalisation capability of both ML and DL models by comparing the predictive distributions between training and test subsets of the AF dataset. A small KL divergence will suggest that the training and test sets are similarly representative of the underlying distribution, corroborating that the sample size is adequate. The following rule of thumb will guide our judgement: if KL divergence < 0.01, the two distributions will be deemed almost indistinguishable; values between 0.01 and 0.1 will imply minor differences, and >0.1 will indicate more substantial differences [90].

Post hoc analyses of (observed) power are admittedly substandard. However, the insights gained from these methods will offer valuable insight into our dataset’s sufficiency given the absence of specific guidance at the time of writing [86].

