Primary: How well does CHA_2_DS_2_-VASc capture 90-day AFAIS recurrence risk in terms of discrimination, calibration, and clinical utility? (Clinical utility performed against updated CPRs, see Tables 3 and 4.) Secondary: How well does CHA_2_DS_2_-VASc capture: 7-day recurrence, 7- and 90-day HT, 90-day decline in functional status, and 90-day all-cause mortality? Exploratory: How well does CHA_2_DS_2_-VASc capture 90-day recurrence and secondary outcomes for non-AF AIS patients?	Primary: Discrimination of CHA_2_DS_2_-VASc for 90-day AFAIS recurrence risk is unsatisfactory (AUC < 0.6), at worst, and modest (<0.7), at best. Calibration for 90-day recurrence also leaves much room for improvement. Secondary: As above.	Discrimination assessed using AUC and calibration curves. Calibration assessed using calibration curves, slopes, and Brier scores. Additional metrics: F1 score, accuracy, precision, sensitivity, specificity, Youden index, PPV, NPR, PLR, NLR.	Primary: A minimum of 680 patients deemed necessary, see Appendix S5.3 in Supplementary Materials file S3. Entire AF dataset will be used, comprising 2763 AFAIS patients. Secondary: As above. Exploratory: Entire non-AF dataset will be used, comprising 7809 AIS patients.	Compute AUCs with 95% CIs using 1000 bootstrap replicates. Produce calibration curves (and report calibration slopes) to illustrate calibration. Calibration curves also serve as alternative to ROC curves, as they illustrate true and false positive rates across different risk thresholds and thus help visualise discrimination. Compute Brier scores. Compute additional metrics.	Discrimination for each outcome will be classified as follows [101]: AUC of 0.81–0.90 = good, 0.71–0.80= fair, 0.61–0.70 = modest, and 0.51–0.60 = poor. In practice, calibration is more vulnerable to geographic and temporal heterogeneity than discrimination [102,103,104,105]. We thus stress that calibration is at least as important as discrimination [77,102]. Clinical utility via DCA will go beyond discrimination and calibration, considering them both at the same time [106], as well as individual preferences.

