##### CPR Development

SHAP will be used to ‘translate’ model insights into CPRs. Mean—and not mean *absolute*—SHAP values will be used in order to preserve information on the directionality of feature importance. The decile rank of each of the eight mean SHAP values from each model will be calculated and a dot plot will be provided to visualise each feature’s mean SHAP value relative to others. (We speak of eight mean SHAP values because we have eight predictor variables corresponding to the features of CHA_2_DS_2_-VASc, namely five comorbid items, sex, and *two* age categories [65–74 years and ≥75 years]). The 25th, 50th, and 75th percentiles of the eight mean SHAP values will be computed. We will subsequently rank the features from most to least important and sort them into three tiers: (1) the lower tier grouping features with mean SHAP values below the 25th percentile, (2) the middle tier grouping features with mean SHAP values between the 25th and 75th percentiles, and (3) the upper tier grouping features with mean SHAP values above the 75th percentile. Features belonging to the lower, middle, and upper tiers will be assigned one, two, and three points, respectively. The purpose of a larger middle tier is to avoid over- or understating the importance of features by promoting stability over frequent changes with minor shifts in model parameters. In the rather unlikely event that one or more features will have negative mean SHAP values and local SHAP value distributions that are consistently left of zero on the beeswarm plots, zero points will be assigned, because their inclusion would degrade 90-day recurrence predictive performance. Ties at quantile cut-points will be resolved conservatively by assigning them to the higher category (e.g., features tied at the 75th percentile will enter the upper tier). The resulting CPRs will be summarised in tabular form and given an acronym in likeness to CHA_2_DS_2_-VASc.

If the dot plot suggests that the distribution of mean SHAP values is very skewed or concentrated, the above-defined tiers will probably inadequately capture features of lower, intermediate, and higher importance. In this eventuality, we will tailor tier boundaries using quantile-based binning. After adapting the tier setup to the observed clusters, we will define lower, middle, and upper tiers whose features will be assigned one, two, and three points, respectively.

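### The 680-patient figure limits overfitting in model development, yet it is used to justify the 691-patient test set and the validation of a fixed score, where it says nothing about precision

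*Protocol article*

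**What the plan says.** Section 2.7 describes a four-step procedure and states that it was devised for developing models from scratch. The third step has the aim to "require minimal regularisation". The results are given as: "The sample sizes derived from steps 1, 2, 3, and 4 were 288, 344, 680, and 459 patients, respectively". The largest is taken as the requirement: "We therefore deemed a minimum total sample size of 680 patients necessary for CPR development". On the inputs, the section says: "We utilised 90-day recurrence rates within the 0.05–0.25 range, conservatively adopting the rate that produced the largest sample sizes". It refers to supplementary material for the remaining inputs, including the anticipated discrimination.

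The figure is then used in two further places:
- Section 2.7, on the hold-out set of 691: "The fact our test set alone exceeds the required 680 patients further supports our sample size".
- Table 1 (section 2.12.4), on validating the existing score: "A minimum of 680 patients deemed necessary, see Appendix S5.3".

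Final evaluation of the models, and the discrimination, calibration and decision curves of the new rules for the primary outcome, rest on the 691-patient test set (Model Evaluation, CPR Evaluation, Table 3). AUC is read in bands of 0.51–0.60, 0.61–0.70, 0.71–0.80 and 0.81–0.90. Table 3 hypothesises fair to good discrimination for the updated rules, which is 0.71–0.90 on that scale. The Introduction says of CHA2DS2-VASc in cohorts with previous stroke that "existing studies have reported poor discrimination, with C-statistics generally below 0.6".

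**The concern.** A shrinkage criterion answers one question: are there enough data to estimate the coefficients without much overfitting? No coefficient is estimated in the test set, and CHA2DS2-VASc has fixed points. What matters in both is how precisely AUC, calibration and net benefit are estimated, and that depends mainly on the number of events. Comparing 691 with 680, or naming 680 as the minimum for validation, therefore supports neither.

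The test set carries the primary comparison of the rules. If recurrence is near the low end of the plan's range, a reader would be told that the test set is comfortably sized when it holds about 35 events.

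A second question is how demanding 680 is for its proper purpose, fitting the logistic model. That depends on the assumed model performance, which drives the binding step.

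**Working it through.** **1. Reproducing the four stated sizes**

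Inputs: recurrence 0.05–0.25 (section 2.7) and P = 8 parameters (CPR Development: "we have eight predictor variables corresponding to the features of" CHA2DS2-VASc). The article does not give the margin, the mean absolute prediction error (MAPE), the shrinkage target S or the Cox-Snell R2. The values below are assumptions chosen because they reproduce the results.

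- Step 1, n = (1.96/0.05)² p(1−p), at p = 0.25: 288.1 (stated 288).
- Step 2, n = exp[(−0.508 + 0.259 ln p + 0.504 ln P − ln MAPE)/0.544], at p = 0.25 and MAPE = 0.05: 343.6 (stated 344).
- Step 3, n = P/[(S−1) ln(1−R2/S)], at S = 0.9 and R2 = 0.10: 8/[(−0.1) ln(1−0.10/0.9)] = 679.2, rounded up to 680 (stated 680).
- Step 4, same formula with S = R2/(R2 + 0.05 × max R2). At p = 0.05, max R2 = 0.328, so S = 0.859 and n = 459.3 (stated 459). At p = 0.10 it gives 314, and at p = 0.25 it gives 221.

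Step 3 contains no recurrence rate once R2 is fixed. The 5% comes from step 4. At 5%, R2 = 0.10 is a Nagelkerke R2 of 0.10/0.328 = 0.31 and an AUC of about 0.86 (linear predictor normal within outcome groups). At 25% the same R2 is an AUC of about 0.71.

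**2. Step 3 requirement at other AUCs (P = 8, S = 0.9)**

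| AUC | 5% recurrence | 10% | 25% |
|---|---|---|---|
| 0.80 | about 1,115 | 605 | 305 |
| 0.75 | 1,707 | 917 | 456 |
| 0.71 | 2,513 | 1,343 | 660 |

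The 2,072 training patients reach the target from AUC about 0.73 at 5% and about 0.67 at 10%.

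**3. Precision in the test set and in the validation set**

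Formulas, with e events and c non-events:
- AUC, Hanley–McNeil: variance = [A(1−A) + (e−1)(Q1−A²) + (c−1)(Q2−A²)]/(ec), where Q1 = A/(2−A) and Q2 = 2A²/(1+A).
- Observed/expected ratio (O/E): SE of log O/E = √[(1−p)/(Np)], interval centred on 1.
- Calibration slope: SE from the information matrix.

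Worked case, N = 691, p = 0.05, A = 0.70: e = 34.55, c = 656.45, Q1 = 0.538, Q2 = 0.576, SE = 0.051, half-width 1.96 × 0.051 = 0.10. For O/E, SE = √(0.95/34.55) = 0.166, so the interval is exp(±1.96 × 0.166) = 0.72 to 1.38.

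| N | Recurrence | Events | AUC half-width | O/E 95% CI | Slope SE |
|---|---|---|---|---|---|
| 691 | 5% | 35 | 0.10 | 0.72–1.38 | 0.24 |
| 691 | 10% | 69 | 0.07 | 0.80–1.25 | 0.18 |
| 691 | 25% | 173 | 0.05 | 0.88–1.14 | 0.13 |
| 2,763 | 5% | 138 | 0.05 | 0.85–1.18 | 0.12 |
| 2,763 | 10% | 276 | 0.04 | 0.89–1.12 | 0.09 |
| 2,763 | 25% | 691 | 0.02 | 0.94–1.07 | 0.07 |

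AUC half-widths and slope SEs are for a true AUC of 0.70. At 5% recurrence, a test-set interval centred on 0.70 runs from 0.60 to 0.80, so it covers both the modest and the fair band.

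**The case against.** **On the training size.** The plan has 2,072 training patients, three times 680, and the logistic model is ridge-penalised with a tuned penalty. Within the hypothesised range the shortfall is confined to recurrence near 5% with AUC 0.71–0.73, where expected shrinkage is still about 0.88–0.90. This stands, and the conclusion on training size survives almost everywhere.

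**On the inferred inputs.** The supplement is not shown, so R2 = 0.10 is a back-calculation and its absence from the article is no fault. It is also not the only fit: shrinkage 0.85 with R2 about 0.064 gives 680, and gives 459 at about 5.2% recurrence, with an AUC of about 0.80. Round values favour 0.9 and 0.10, but that is inference.

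**On a contradiction with the plan's own expectations.** A reader might infer that an AUC of 0.86 conflicts with the C-statistics below 0.6 in the Introduction. The documents do not support that. Those figures concern the fixed score, whereas the update re-estimates weights, recodes age and adds earlier stroke, and 0.86 lies inside the hypothesised range. The claim of a conservative choice is worded about the recurrence rate, not about model performance.

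**On the validation and test samples.** The 2,763-patient validation is reasonably precise, so Table 1 does no practical harm beyond a wrong justification. Model AUCs are also compared by DeLong's method on the same patients, so the separate intervals overstate uncertainty about differences. At 25% recurrence the test-set half-width falls to 0.05. These points stand, but none makes 680 a valid yardstick for the test set or for a fixed score.

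**Conclusion.** The misuse of 680 holds on the text alone. Section 2.7 derives it for development, then applies it to the test set, and Table 1 applies it to validating a fixed score. The consequence depends on the recurrence rate. It is serious for the test set near 5% (about 35 events, AUC ±0.10, O/E 0.72–1.38), moderate at 10% and modest at 25%. The full validation sample is adequate on its own merits.

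The size of 680 itself is a lesser point. Its most plausible input is optimistic if recurrence is near 5%, but not inconsistent with the plan. Two stronger readings do not follow: that the regression training set is inadequate in general, or that the test set can never distinguish the AUC bands. Both apply only towards the low end of the plan's recurrence range.

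The results rest on eight parameters, a shrinkage target of 0.9, an approximately normal linear predictor within outcome groups, and the plan's own recurrence range.

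**What to change.** - In section 2.7, delete the sentence that compares the test set with 680. In Table 1, remove 680 as the minimum for validation.
- In their place, give the expected number of events and the interval widths for AUC, O/E (or its inverse, which the plan already reports) and calibration slope, for the 691 test patients and the 2,763 validation patients, over recurrence 0.05–0.25.
- State the R2 and shrinkage target behind 680 beside the figure. Show the required training size over the same recurrence range and a plausible AUC range, and say where 2,072 is enough.
- Optionally, report the out-of-fold performance from the nested cross-validation already planned within the 2,072 training patients alongside the test-set result.

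The cost is less favourable stated figures and a little computing. No extra patients are needed, and no planned analysis has to be replaced.
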